### Secondary Outcomes

For the evaluation of secondary outcomes, we will use the statistical methods described above to evaluate both the immediate and medium-term effects of the SAS video intervention. The methods include, but are not limited to, *t* tests for independent groups, matched *t* tests for dependent groups, repeated measure ANOVAs, and multilevel regression models. For that, we will analyze the mean scores of the stigma surveys at T1 and T2, with a focus on the impact of the SAS video intervention on the score outcomes. All analyses will be conducted in R.

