### Randomization, Consent, and Study Design

After reviewing the Institutional Review Board-approved information sheet, delivered to prospective participants online via ProA, those who indicate their consent to take part in the study will then be randomly assigned to one of three groups:

Intervention A: receiving the SAS video full intervention group.Intervention B: receiving the SAS video partial intervention (without sound) group.Control Group: receiving written information about addiction prevalence.

A baseline survey will be used to collect demographic information as well as baseline data on our primary and secondary outcomes. Thereafter, the Intervention A group will watch the 2.5-minute video, the Intervention B group will watch the 2.5-minute video without sound, and the control group will read a fact sheet about the global burden of addiction. Following this, all groups will complete a series of validated questionnaires to assess our primary outcome: addiction stigma, and secondary outcomes: optimism, warmth toward the subject, and hopefulness.

We will conduct the first round of surveys immediately post exposure of the intervention groups to the SAS video interventions and the control group to their written fact sheet. Follow-up assessments, using the same surveys, will be conducted 2 weeks later. To ensure the accuracy and validity of the results, we will include attention checks and exclude participants who fail these checks. Each participant will spend approximately 8 minutes watching the intervention and completing the surveys and will receive US $4.80 for completing the study. Figure 1 represents the trial design and flow.

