#### Analysis

At the first time point (T1), we will compare addiction stigma, optimism, hope, and warmth toward subject scores between the 2 intervention groups and the control group. This comparison is intended to establish the immediate effect of watching the intervention videos on addiction stigma, optimism, hope, and warmth toward people with addiction. At the second time point (T2), we will once again compare our primary and secondary outcomes between the intervention and control groups. This will allow us to detect potential short-term effects of watching the intervention video on addiction stigma, optimism, hope, and warmth toward people with addiction. By comparing the outcomes of the 2 intervention arms at the 2 time points, we will be able to measure the contribution of sound design to the effect of the SAS video intervention.

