#### Sequence Generation, Allocation Concealment, and Implementation

This 3-arm individual, parallel-group randomized controlled online trial will be hosted and implemented by the Qualtrics survey platform. The platform uses a computer-generated allocation sequence to randomly allocate participants 1:1:1 to the 3 trial arms. The investigators will remain unaware of individual trial arm allocations.

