##### Primary Outcomes

For each participant, stigma scores will be calculated individually. The mean score for each study arm at T1 and T2 will be calculated and compared between the intervention arms and the control arm at T1, and between the intervention arms and the control arm at T2, using repeated measure ANOVAs. This will be done at the study level and the country level to identify differential effectiveness across geographic conditions. We will also use multilevel regression analyses to control for demographic factors and other potential variables as needed. All analyses will be conducted in R (R Core Team, 2021).

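### For the secondary outcomes, matched t tests are listed as a way to evaluate the video's effect, although they can only test change over time, which the control arm may share

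*Protocol article*

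**What the plan says.** The Secondary Outcomes section of the statistical methods gives its methods one purpose: "to evaluate both the immediate and medium-term effects of the SAS video intervention". The list is open and begins with a valid between-arm test: "The methods include, but are not limited to, *t* tests for independent groups". Next comes "matched *t* tests for dependent groups", followed by repeated measures ANOVA and multilevel regression. The matched test is given no separate or descriptive role. On the data to be used, the section says "we will analyze the mean scores of the stigma surveys at T1 and T2".

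Three other places bear on the point:

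- The Analysis section defines the comparisons between arms, for secondary outcomes too. At T2, for example, "we will once again compare our primary and secondary outcomes between the intervention and control groups". It also compares the two intervention arms with each other at both time points.
- The Primary Outcomes section has stigma scores "compared between the intervention arms and the control arm at T1", and likewise at T2.
- The section on sequence generation describes "This 3-arm individual, parallel-group randomized controlled online trial". The section on randomization and study design says that the baseline survey collects "baseline data on our primary and secondary outcomes".

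**The concern.** The effect that the trial sets out to estimate is a difference between randomised arms. Each arm consists of different people and no matching across arms is described, so the only dependent scores are one participant's repeated measurements. The protocol does not say that the matched test is run within an arm. That is an inference from the design, but pooling the arms would leave the same null hypothesis of no change over time. Either way, control does not enter as a comparator.

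The participants answer the same instruments before exposure, shortly after it and again 2 weeks later. Familiarity with the items, wanting to please the researchers, or regression to the mean could move every arm alike. A matched test in a video arm that starts from baseline would count this movement as if the video had caused it. A matched test from T1 to T2 starts after exposure. It describes fading, not the effect against control.

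At stake is a secondary claim on optimism, warmth or hope that rests on a within-arm p-value although the control arm changed by the same amount. With arms this large, a very small shared drift is enough.

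**Working it through.** The plan states no figure for the matched test, so there is none to reproduce. The check asks how often such a test rejects when the video does nothing and all arms drift equally.

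**Inputs from the protocol (Sample Size section).** 1500 recruited per arm per country; 20% attrition; one-tailed alpha 0.01. Baseline-T1 pairs come from one session, so n = 1500. Pairs that use T2 need T2 completers: 1500 × 0.8 = 1200 per arm per country, or 3 × 1200 = 3600 pooled over the countries.

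**Assumed inputs (not in the protocol).** Shared drift m = 0.05 SD in the hypothesised direction, with 0 and 0.10 SD for range; within-person correlation ρ = 0.5, 0.7 and 0.8; equal SD of 1 at both times; no video effect.

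**Formula.** The SD of a change score is √(2(1−ρ)), so SE = √(2(1−ρ)/n). By normal approximation, the one-sided 0.01 matched test rejects with probability 1 − Φ(2.326 − m/SE).

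**Worked example** (m = 0.05, ρ = 0.7, n = 1200): SE = √(0.6/1200) = 0.02236; m/SE = 2.236; 1 − Φ(0.090) = 46%.

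**Rejection rate at 0.05 SD shared drift, no video effect**

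| Pairs | n per arm | ρ = 0.5 | ρ = 0.7 | ρ = 0.8 |
|---|---|---|---|---|
| Baseline-T1, one country | 1500 | 35% | 57% | 77% |
| Using T2, one country | 1200 | 28% | 46% | 66% |
| Using T2, three countries pooled | 3600 | 75% | 94% | 99% |

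With zero drift every cell is 1%. With 0.10 SD drift and n = 1200 the rates are 87%, 98% and 99.9%. A two-sided 0.01 test at 0.05 SD and n = 1500 gives 26%, 47% and 69%, and it would reject for drift in either direction.

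**Comparison with a between-arm test.** 4000 simulated trials per drift value, n = 1200 per arm, ρ = 0.7, one-sided 0.01, no video effect:

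| Shared drift | Matched test, video arm | Matched test, control arm | Video arm significant, control not | Between-arm t test on change |
|---|---|---|---|---|
| 0 | 0.9% | 1.3% | 0.9% | 0.98% |
| 0.05 SD | 45.5% | 46.0% | 24.9% | 0.88% |
| 0.10 SD | 98.4% | 98.6% | 1.4% | 0.88% |

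The control arm passes the matched test as often as the video arm. At 0.05 SD, about a quarter of the runs show the video arm significant and the control arm not, although nothing differs between them. The between-arm test stays at about 1% throughout.

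**The case against.** The strongest reply is that the plan already defines the effect between arms. The Analysis section does so for stigma, optimism, hope and warmth at T1, for primary and secondary outcomes at T2, and for the two video arms against each other. The sentence at issue is an open list of tools that puts independent t tests first and ties no contrast, time pair or claim to the matched test. This stands. A reader might infer that the randomised comparison is abandoned for the secondary outcomes, or that no valid test is planned; the documents do not support either. What remains is that the list has a stated purpose, evaluating the video's effects, and the matched test cannot serve it. Nothing in the section says which method carries the claim. A method has been named for the wrong purpose; this is more than detail left to an analysis plan.

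Second, a T1-T2 matched test gives a null result when an effect fully persists, and a reader might count that as an error. It is not one: the test is about fading, and the planned T2 comparison between arms addresses whether an effect is still present.

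Third, the section speaks of stigma surveys, and a reader might infer that the primary outcome is affected. The Primary Outcomes section specifies its own between-arm comparison, so it is not.

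Fourth, the rates rest on assumptions. The documents give neither drift nor correlation, and the one-sided 0.01 is borrowed from the sample-size calculation for comparing arms. The section names only T1 and T2, so baseline-T1 pairs are possible but not stated. For pairs using T2, the n = 1200 figures apply and the higher n = 1500 figures do not. One-sided inflation also needs drift in the favourable direction. All of this limits the size, but the mechanism does not depend on it.

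**Conclusion.** The point holds for the secondary outcomes only. A test whose null is no change over time is admitted, next to valid between-arm methods, as evidence of the video's effect. Under no video effect and a shared favourable drift of 0.05 SD, with correlation 0.5 to 0.8 and one-sided 0.01, it rejects about 35% to 77% of the time per country for baseline-T1 pairs and about 28% to 66% for pairs using T2. A between-arm test of change rejects about 1%. These rates illustrate the mechanism and do not forecast this trial's error rate; with no drift the matched test rejects at its nominal 1%. The wording should be corrected because a within-arm p-value could otherwise be presented as an effect of the video, but neither the primary analysis nor the planned between-arm comparisons are in doubt.

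**What to change.** In the Secondary Outcomes section of the statistical methods:

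- Remove matched t tests from the methods for evaluating the effects of the SAS video.
- State that effect claims on optimism, warmth and hope rest on the between-arm contrasts already set out in the Analysis section (A vs control, B vs control, A vs B) at T1 and at T2.
- State that claims about durability rest on the between-arm difference in change (arm by time).
- Show within-arm change only descriptively, as means with confidence intervals for all three arms.

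The cost is a sentence or two of wording and no new data. The only loss is the within-arm p-values, which do not answer the trial's question.

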### Primary Outcome

The primary outcome is stigma toward people with addiction, which we will measure using an abbreviated, 18-item version of the Attribution Questionnaire (AQ-18) [25,26]. This version (AQ-18) includes the blame, pity, help, dangerousness, fear, and avoidance subscales of the original questionnaire, as these subscales are most appropriate, in scope and topic area, to detect a potential effect of our short video “micro-intervention.” The AQ-18 will be scored along a 9-point Likert scale indicating the extent to which participants agree with the item ranging from “not at all” (1) to “very much” to (9) with a maximum score of 27 for each 3-item construct. Higher scores indicate greater stigma. The AQ-18 is highly reliable and subscales have Cronbach *α* ranging from fair (0.6, responsibility) to good (0.93, fear/dangerousness) [25,26]. Participants responding to the AQ-18 may score between 12 and 108. Like the longer version, the AQ-18 offers a brief vignette, which we modified to be (1) gender-neutral and (2) about addiction rather than general mental illness. All participants will read the following vignette before completing the questionnaire. A gender-neutral name (Alex) was chosen to eliminate potential gender bias:

Alex is a 30-year-old with a history of addiction. Alex’s substance use problem has harmed Alex’s health and hurt others. Alex has been hospitalized several times for addiction-related health problems.

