#### Attitude

We will also measure attitudes toward those with addiction using a “stigma thermometer,” a tool we previously developed to assess attitudes regarding sexual orientation and gender diversity [28]. The thermometer provides the following prompt:

Using a scale from zero to 100, please tell us about your personal feelings toward people who are addicted to substances such as drugs or alcohol. As you do this task, think of an imaginary thermometer. The warmer or more favorable you feel toward people who are addicted to substances such as drugs or alcohol, the higher the number you should give it. The colder or less favorable you feel, the lower the number. If you feel neither warm nor cold toward people who are addicted to substances such as drugs or alcohol, rate it 50.

Researchers in the fields of political science and psychology have frequently used feeling thermometers to assess attitudes toward stigmatized groups [29].

Finally, we will measure subjective levels of hope using a visual analog scale (VAS), a longstanding, validated tool for assessing related constructs of stress and subjective well-being [30]. The VAS provides the following prompt:

Using a scale from zero to 100, please tell us about how hopeful you feel after watching the video [control group participant instructions will reference the fact sheet in the AQ-27 instead]. As you do this task, think of an imaginary thermometer. The more hopeful you feel, the higher the number you should give it. The less hopeful you feel, the lower the number. If you feel neither hopeful nor hopeless, rate it 50.

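### The secondary-outcome analysis section names the wrong scores and leaves an open list of tests, so no single randomised comparison is fixed for optimism, warmth or hope

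*Protocol article*

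**What the plan says.** The Primary Outcome section assigns stigma to the primary role: "The primary outcome is stigma toward people with addiction, which we will measure using an abbreviated, 18-item version of the Attribution Questionnaire". Randomization, Consent, and Study Design lists the others as "secondary outcomes: optimism, warmth toward the subject, and hopefulness". Their instruments are the BIOS-G (4 to 16), a 0–100 warmth thermometer and a 0–100 hope VAS.

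The Analysis section says that at T1 "we will compare addiction stigma, optimism, hope, and warmth toward subject scores between the 2 intervention groups and the control group". It repeats the comparison at T2 for the primary and secondary outcomes, and compares the two video arms to isolate the effect of sound.

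Among the statistical methods, the Secondary Outcomes section opens: "For the evaluation of secondary outcomes, we will use the statistical methods described above to evaluate both the immediate and medium-term effects". It continues with "The methods include, but are not limited to", followed by independent t tests, matched t tests, repeated-measures ANOVAs and multilevel regression. It then names the data: "For that, we will analyze the mean scores of the stigma surveys at T1 and T2".

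**The concern.** There are two faults, and both lie in what the section states.

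First, the scores it names belong to the primary construct. BIOS-G and the hope VAS are not stigma surveys on any reading, so the sentence does not match the outcomes that its own heading announces.

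Second, the list of methods is open by its own words, and its members answer different questions. An independent t test is a comparison between randomised arms. A matched t test is a change within one arm and makes no use of the randomisation. Either could be reported as the effect of the video on optimism, warmth or hope.

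What is at stake is the credibility of the secondary claims. The Sample Size section sets a Type I error of 0.01 to allow for multiple comparisons. Nothing there covers a choice among several analyses of the same contrast.

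**Working it through.** **Step 1: which scores are analysed.** The sections compare as follows.

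| Section | Scores named |
|---|---|
| Primary Outcome | stigma (AQ-18) as primary |
| Randomization, Consent, and Study Design | optimism, warmth, hopefulness as secondary |
| Analysis | stigma, optimism, hope and warmth at T1; primary and secondary outcomes at T2 |
| Secondary Outcomes (statistical methods) | the stigma surveys |

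The last row disagrees with the two above it. Warmth can arguably be rescued, because the article calls its instrument a stigma thermometer: "We will also measure attitudes toward those with addiction using a “stigma thermometer". Optimism and hope cannot. Two of the three secondary outcomes are outside the scores named.

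**Step 2: which method is fixed.** The section refers back to methods already described. The Primary Outcomes analysis section describes repeated-measures ANOVA and multilevel regression only. The two t tests are new, and the list is declared incomplete. The back-reference therefore does not lead to one method.

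**Step 3: how much a free choice could matter.** The plan gives no figure to reproduce here, so this is an illustration.

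Inputs:
- No true effect and one contrast between two arms at T1.
- Correlation r between an outcome's baseline and T1 values: an assumption, taken from 0.5 to 0.85, because the article gives none.
- Three analyses that the open list admits: post score, change score, baseline-adjusted score.

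Let B and Y be the standardised arm differences at baseline and T1. In large samples the three test statistics are:
- post score: z1 = Y
- change score: z2 = (Y − B) / √(2 − 2r)
- baseline-adjusted: z3 = (Y − rB) / √(1 − r²)

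Their correlations are corr(z1, z2) = √((1 − r)/2), corr(z1, z3) = √(1 − r²) and corr(z2, z3) = √((1 + r)/2). At r = 0.5 these are 0.50, 0.87 and 0.87. At r = 0.85 they are 0.27, 0.53 and 0.96. The tests overlap but are far from identical.

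The chance that at least one is significant, by simulation with 4,000,000 null draws per value of r, is:

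| r | two-sided 0.01 | two-sided 0.05 |
|---|---|---|
| 0.5 | 2.1% | 9.7% |
| 0.7 | 2.2% | 10.1% |
| 0.85 | 2.2% | 10.3% |

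The sample size formula is one-sided at 0.01. On that basis the same calculation gives 2.0% to 2.2%. The ceiling for any three tests is 3 × 1% = 3%, or 3 × 5% = 15%.

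**Step 4: limit for hope.** The hope prompt asks how hopeful the participant feels after the video, or for controls with reference to the fact sheet. The article plans baseline data on the secondary outcomes, but that wording cannot be put unchanged before exposure. If hope has no comparable baseline, the change-score and baseline-adjusted options fall away, and the table does not apply to it.

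**The case against.** A reader might infer from the stigma sentence that optimism and hope have no stated analysis at all. The documents do not support that. The Analysis section names both for comparison with control at T1 and covers them at T2, and the Secondary Outcomes section opens by applying the methods described above to secondary outcomes. The wrong noun is a conflict between sections, not an absence of analysis.

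A reader might also see a second route to a positive result on the primary outcome. That is weak: stigma has its own analysis section, and a t test reported under secondary outcomes would not become the primary result.

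On size, the objection is that the section names neither a change-score test nor a baseline-adjusted model. That is correct. They enter only because the list is open and because the regression described for the primary outcome may control for further variables as needed. A wider set that adds the average of T1 and T2 gives 2.5–2.7% at 0.01 and about 11.5–12% at 0.05. But that average is a different quantity from the separate T1 and T2 comparisons the plan describes, so the larger figures mix choice of method with choice of time point and should not be used.

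Finally, model detail commonly sits in a statistical analysis plan, which is not shown. This stands for covariates and model form. It does not excuse a wrong outcome name or an express statement that the methods are not limited to those listed. An analysis plan would have to contradict this sentence to correct the outcome name. The article also says that it is itself the full protocol, so no longer protocol can be expected to settle the point.

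**Conclusion.** The point holds in two parts. The secondary-outcome section names the primary construct's surveys as its data, in conflict with the design and Analysis sections. It also leaves an open list that mixes within-arm and between-arm tests, so no one randomised comparison is fixed for any secondary outcome.

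The error figures are illustrative. They rest on an assumed correlation of 0.5 to 0.85, a free choice among three T1 analyses, and a usable baseline. On those terms the error of one contrast roughly doubles. The inflation comes on top of any multiplicity across outcomes, time points and arms.

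The weight is moderate to minor. Only secondary claims are affected, but the correction is cheap and is best made before any data are seen. The article reports that none had been collected as of March 2025.

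**What to change.** 1. In the data sentence, replace the stigma surveys with the BIOS-G, warmth thermometer and hope VAS scores at T1 and T2.
2. Delete the phrase that leaves the list open.
3. Name one main between-arm analysis per secondary outcome: a linear model at each time point with arm and country, plus the outcome's own baseline where it is measured comparably. Country belongs in the model because the Abstract describes randomisation per country, and the baseline survey is already planned. Report from it the contrasts the Analysis section already sets out: each video arm against control, and video with sound against video without.
4. State whether hope has a comparable baseline. If it does not, fit its model without one.
5. Label independent t tests, repeated-measures ANOVAs and other models as sensitivity analyses, and matched t tests as descriptive.

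The cost is a few sentences of text, with no change to data collection or sample size. The investigators give up a free choice of method for the secondary outcomes.
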